# A placebo-controlled, crossover trial to investigate the efficacy of tiotropium bromide or placebo added to usual care in stable symptomatic post-hematopoietic stem cell transplantation (HSCT) bronchiolitis obliterans syndrome (BOS)

**DOI:** 10.1186/s13063-024-08051-7

**Published:** 2024-04-06

**Keywords:** Bronchiolitis obliterans, Obstructive lung function, Tiotropium

## Abstract

**Background:**

Despite the fundamental progress in hematopoietic stem cell transplant, this treatment is also associated with complications. Graft-versus-host disease is a possible complication of HSCT. Bronchiolitis obliterans syndrome (BOS) is the pulmonary form of this syndrome. Due to the high morbidity and mortality rate of BOS, various studies have been conducted in the field of drug therapy for this syndrome, although no standard treatment has yet been proposed. According to the hypotheses about the similarities between BOS and chronic obstructive pulmonary disease, the idea of using tiotropium bromide as a bronchodilator has been proposed.

**Method/design:**

A randomized, double-blind, placebo-controlled, and crossover clinical trial is being conducted to evaluate the efficacy of tiotropium in patients with BOS. A total of 20 patients with BOS were randomly assigned (1:1) to receive a once-daily inhaled capsule of either tiotropium bromide (KP-Tiova Rotacaps 18 mcg, Cipla, India) or placebo for 1 month. Patients will receive tiotropium bromide or placebo Revolizer added to usual standard care. Measurements will include spirometry and a 6-min walking test.

**Ethics/dissemination:**

This study was approved by the Research Ethics Committees of Imam Khomeini Hospital Complex, Tehran University of Medical Science. Recruitment started in September 2022, with 20 patients randomized. The treatment follow-up of participants with tiotropium is currently ongoing and is due to finish in April 2024. The authors will disseminate the findings in peer-reviewed publications, conferences, and seminar presentations.

**Trial registration:**

Iranian Registry of Clinical Trial (IRCT) IRCT20200415047080N3. Registered on 2022–07-12, 1401/04/21.

**Supplementary Information:**

The online version contains supplementary material available at 10.1186/s13063-024-08051-7.

## Background

Pulmonary complications account for more than 90% of mortality after bone marrow transplant (BMT). Bronchiolitis obliterans syndrome (BOS) is one of them, which is defined as the pulmonary form of graft-versus-host disease (GVHD). Due to post-bone marrow transplant bronchiolitis obliterans syndrome (PBMTBOS), high morbidity and mortality rate, various studies have been conducted in the field of drug therapy [1], although no standard treatment has yet been proposed [2, 3].

Different treatments have been investigated for this disease, but if new bronchiolitis obliterans have been diagnosed, azithromycin, along with immunosuppressant and adjustment of the immunosuppressant regimen, is one of the therapeutic strategies [2–9].

Systemic corticosteroids, along with other immunosuppressive drugs, are known as the core of treatment in BOS [2]. Clinical studies conducted so far have not seen a significant effect on the treatment of patients by adding azathioprine, mycophenolate, thalidomide, and hydroxychloroquine [10–12]. On the other hand, a 2002 study by Koc et al. concluded the use of cyclosporine as corticosteroid-sparing can be considered [13].

Bergeron et al., in 2014, in a randomized، double-blind clinical trial on PBMTBOS, evaluated the possible effect of budesonide/formoterol in these patients. In this study, the FEV1 saw an increase in the treatment group [14].

In another study conducted in 2005 by Khalid et al., the effect of azithromycin on PBMTBOS was evaluated. Based on the results of this study, patients showed an increase in forced vital capacity and FEV1 compared to baseline [15]. Also, in another study conducted by Vos et al., in post lung transplant BOS (PLTBOS), the results showed that long-term use of azithromycin can reduce the rate of drop in FEV1 in patients [16].

Williams and colleagues evaluated the effect of fluticasone/azithromycin/montelukast regimens in a 2016 study on patients with PBMTBOS. The study reported significant improvements in FEV1, functional status, and life satisfaction in patients [17].

Due to the different possible processes in disease pathogenesis, several studies have investigated the role of TNF-alpha inhibitors as well as drugs such as imatinib and ruxolitinib [2]. In a study conducted by Zeiser et al. on 41 patients with chronic GVHD on the efficacy of ruxolitinib, the results of the study showed an improvement in respiratory symptoms in 4 patients with respiratory GVHD in this study [18]. In another study by Olivieri and colleagues on the possible benefits of imatinib in the treatment of 19 patients with chronic GVHD, 7 out of 11 patients with pulmonary involvement showed improvement in respiratory function [19].

Few studies evaluated the effect of tiotropium in the treatment of BOS. In 2014, Kawassaki and colleagues investigated the possible impact of tiotropium bromide on the treatment of patients with secondary constrictive bronchiolitis due to various causes. In this study, 11 patients with constrictive bronchiolitis were treated with tiotropium bromide for an average of 21 days (with a minimum treatment period of 14 days), and spirometry tests were evaluated before and after treatment in the patients. According to the results of this study, FEV1 saw a rise. Also, FVC levels increased, although no significant difference was observed in FEV1/FVC levels. This study was conducted without a control group, and the results were only compared before and after the intervention [20].

Bronchiolitis obliterans (BO) is believed to be caused by a myriad of reasons like infection, post-toxin exposure, post HSCT and post lung transplant. Following the data, however, somehow in PLTBOS, fibrosis might be made and the treatment might be different. But generally speaking, BO refers to the small-airway epithelial cells and subepithelial structure changes which cause excessive fibroproliferation due to aberrant tissue repair. The disease is mentioned to cause air trapping, mosaic attenuation, and hyperinflation and is defined as an obstructive pulmonary function. The disease is pure obliteration of the small airways (< 2 mm) [5, 21].

All in all, for patients with bronchiolitis obliterans who have undergone HSCT or lung transplantation, several immunosuppressive medications and immune-modulating treatments have been reported to stabilize pulmonary function in BOS patients in some trials. Low-dose macrolide antibiotics (azithromycin), leukotriene-receptor antagonists (montelukast), and combinations of inhaled bronchodilators and glucocorticoids are believed to help BOS symptoms and halt the decrease in pulmonary function tests [21], but more studies are needed to find the best protocol for disease management.

Tiotropium is an anticholinergic drug that is used in the management of chronic obstructive pulmonary disease (COPD) and is believed to have anti-inflammatory effects as well [22]. It has been studied in post-infectious and post-HSCT BOS and a decrease in airway obstruction and improvement in lung function was reported [23, 24]. According to the hypotheses about the similarities between BOS and COPD, the idea of using tiotropium bromide as a bronchodilator has been proposed. This is to observe and evaluate the changes of % FEV1 with the tiotropium add-on therapy.

## Methods/design

### Study design

This is a randomized, double-blind, placebo-controlled, crossover trial of maintenance treatment with once-daily tiotropium for patients with BOS. The study will be conducted in two general educational hospitals. This paper presents the design and protocol for the trial according to the Standard Protocol Items: Recommendations for Interventional Trials (SPIRIT) statement (Supplementary Material 1) [25]. An overview of the study design and timeline for participants is provided in Fig. 1.

**Fig. 1 Fig1:**
[figure not shown]
Study design overview

The crossover design will consist of two sequences with two treatment periods (AB/BA or BA/AB) each lasting 1 month and separated by a 1-week wash-out period. In treatment period A or B, patients will receive tiotropium bromide or a placebo Revolizer added to usual standard care. Patients will be screened for eligibility and, once confirmed, will be randomized (1:1) to each treatment sequence. After completing the first treatment period in the sequence, patients will undergo a 1-week wash-out period in which they receive only the usual standard care. Then, they will receive the alternative treatment period which they have not received yet. Patients allocated to treatment sequence 1 will receive treatment period A, then wash-out period, and then treatment period B; patients randomized to treatment sequence 2 will receive treatment period B, then wash-out period, and then treatment period A.

Patients who are referred to pulmonary clinics will be screened for eligibility criteria. Baseline data must be collected before enrollment. Baseline data include age, gender, time from transplantation, time from diagnosis of BOS, prior and current immunosuppressive and topical respiratory medication history, other medications, NIH lung symptom score, and chronic GVHD activity in other organs. Spirometry and a 6-min walking test (6MWT) must be performed before enrollment. All patients are required to complete a 36-Item Short Form Survey (SF-36), Cough Quality-of-Life Questionnaire (CQLQ), and St. George’s Respiratory Questionnaire (SGRQ) before enrollment.

A total of 20 eligible patients will be enrolled in the trial. Central computerized permuted blocked randomization will be performed using a 1:1 allocation schedule with random block sizes of 4. The randomization process is performed by investigators who are neither involved in participant recruitment, nor study conduct and assessment evaluation. The allocation sequence will be concealed from the researchers using sequentially numbered, opaque, and sealed envelopes.

During the treatment period A, patients will receive inhaled tiotropium bromide (KP-Tiova) at a dose of 18 mcg once daily in the morning plus usual standard care. Standard usual care consists of inhaled corticosteroids and long-acting beta-2 agonists in a fixed combination in the formulation and dosage which were prescribed to the patient before study enrollment. Other immunosuppressive or GVHD modifying agents must be administered through the study at a dose similar to the study onset. All the patients must be instructed regarding the self-administration of study treatment at the onset of the trial.

During the treatment period B, patients will receive a tiotropium bromide placebo Revolizer plus standard usual care. The placebo Revolizer is identical to the experimental Revolizer in appearance, smell, taste, and texture and is administered on the same schedule as the experimental treatment.

In the wash-out period, patients receive only standard usual care as above. The wash-out period is supposed to last 1 week.

Patients will continue to receive study schedules until completion of the trial, occurrence of unacceptable adverse events, progressive pulmonary disease, change in immunosuppressive agents due to alterations in GVHD activity in other organs, malignancy relapse or graft failure, and withdrawal of consent.

Assessments will be performed at the end of the first treatment period, at the end of the wash-out period, and at the end of the second treatment period. Assessments include spirometry, 6MWT, NIH lung symptom score, GVHD activity in other organs, SF-36 score, SGRQ score, CQLQ score, VAS score, and monitoring of adverse events.

### Eligible participants

The outpatient BOS cases of the pulmonology clinic of Shariati Hospital and Taleghani Hospital were selected. Patients to be enrolled are required to meet all inclusion criteria listed in Table 1 and not meet any of the exclusion criteria. Those with BOS patients with baseline 20% ≤ %FEV1 < 70% will be selected and contacted by telephone. The eligible participants will be asked to visit the research center.

**Table 1 Tab1:** Inclusion and exclusion criteria

Exclusion criteria	Inclusion criteria
1) Life expectancy < 6 months at the time of enrollment as judged by the enrolling investigator	1) Subjects able to sign the Informed Consent
2) The need for chronic oxygen therapy	2) 18 years of age or older
3) Baseline %FEV1 ≤ 20%	3) Diagnosis of post-HSCT-BOS according to NIH 2014 criteria
4) History of thoracic air leak syndrome	4) Baseline %FEV1 < 70%
5) Documented respiratory infection	5) Must be symptomatic, defined as NIH Lung Score 1–3, and no other contributing etiology (including cardiac diseases, infection, anemia, or extrinsic thoracic compression) is present for respiratory symptoms
6) Active malignancy	6) Stable disease defined as less than 10% change in %FEV1 during the past 3 months while having no change in immunosuppressive and topical respiratory medications in the past 3 months
7) Graft failure	7) Must have received a combination of inhaled corticosteroid and inhaled long-acting beta-2 agonist during the past 3 months
8) Known history of asthma or chronic obstructive lung disease (COPD)	8) No new or supplemental immunosuppressive therapy for extra-thoracic GVHD during the past 3 months
9) Active smoking during the past 12 months	9) Patients with prior exposure to short-acting or long-acting inhaled anti-cholinergic drugs are eligible unless they have been received within the past 3 months
10) Substance abuse or uncontrolled psychiatric disorder	10) Ability to use Revolizer
11) Pregnant or nursing women	
12) Daily corticosteroid of more than 1 mg/kg prednisone equivalent	
13) Known intolerance or allergy to anticholinergic drugs	
14) History of urinary retention, angle-closure glaucoma, CrCl ≤ 30 ml/min	
15) History of arrhythmia in past years, MI in past 6 months, or hospital admission due to heart failure in past year	
16) Ongoing participation in any other clinical trial (more typical would be using an investigational agent within 28 days of enrollment)	
17) Any condition that, in the opinion of the enrolling investigator, would interfere with the subject's ability to comply with the study requirements	
18) Inability to perform pulmonary function tests (PFT) reliably, as determined by the enrolling investigator or PFT lab	
19) No compliance	

### Follow-up and duration of the study

There will be 4 visits, one baseline, one after 1 month of being included, another one after passing the washout period which is the time of being included in the next period, and the last one is going to be 1 month after. An overview of the measures used at each of the four time points is illustrated in Table 2. To improve the compliance of patients, the strategies are as follows: adhere to the principle of voluntary participation and explain the benefits of this study to the participants and the importance of treatment and adherence to the treatment. The health education process could increase the related knowledge, change the behavior, and enhance the compliance of the patient, but they were excluded if they did not have enough adherence and did not use more than 25% of their drug in the previous period. If a patient chooses not to complete trials, they will participate routinely in pulmonary clinics and will directly be monitored by our pulmonologists they will be excluded from the trial. Tiotropium is a routine drug that is prescribed; therefore, it has known side effects and our pulmonologists are familiar with them. Written informed consent will be obtained from each patient before they begin the trial. All participants will fill in informed consent.

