### Adverse events

The adverse events will be examined by open questions, as well as symptoms, and by precise questions about the potentially related adverse effects of the tiotropium which was used in the trial, as xerostomia, pharyngitis, and cardiovascular events like hypertension, edema, and chest pain, etc. The rate of adverse effects will be determined by linking the frequency of adverse events in the experimental drug and placebo by calculating the NARAJNJO scale***.***

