### Statistical methods

The analysis will be done by intention-to-treat and per-protocol. Assessment for various effects in the cross-over design will be performed via the following statistical methods:Treatment effect (comparison between the intervention and control) will be investigated by paired *t*-test.Period effect (the effect of the same treatment received at two different periods is different for each period) will be assessed by the *t* statistics, as follows:$$t=\frac{ {dY}_{\mathrm{diff }\ \left(T-P\right)}- {dY}_{{\mathrm{diff}}\ \left(P-T\right)}}{\sqrt{^{{{\text{SD}}}_{\left(T-P\right)}^{2}}\!\left/ \!_{ {n}_{(T-P)}}\right.+^{ {{\text{SD}}}_{\left(P-T\right)}^{2}}\!\left/ \!_{ {n}_{(P-T)}}\right.}}$$where *dY*_diff(*T*–*P*)_ is the mean difference in changes of “endpoint Y” in treatment sequence followed by placebo, SD^2^_(*T*–*P*)_ was the variance of the difference of “endpoint Y” and *n*_(*T*–*P*)_ was the number of patients in this sequence. Definitions for the *P*–*T* sequence are the same.Period-by-treatment interaction (whether the two treatment effects are different in the two periods), will be evaluated by the t statistic as follows:$$t=\frac{ {\mathrm{total}\ \mathrm{Mean}\ dY}_{ \left(T-P\right)}- {\mathrm{total}\ \mathrm{Mean}\ dY}_{ \left(P-T\right)}}{\sqrt{^{{{\text{SD}}}_{\mathrm{total}\ \mathrm{Mean}\ \left(T-P\right)}^{2}}\!\left/ \!_{ {n}_{(T-P)}}\right.+^{ {{\text{SD}}}_{\mathrm{total}\ \mathrm{Mean}\ \left(P-T\right)}^{2}}\!\left/ \!_{ {n}_{(P-T)}}\right.}}$$In which:$${\mathrm{total}\ \mathrm{Mean}\ dY }_{(T-P)}= \frac{\sum_{1}^{n}{\mathrm{individual\ Mean}\ dY}_{(T-P)}}{{n}_{(T-P)}}$$And:$${\mathrm{individual\ Mean}\ dY}_{(T-P)}=\frac{{dY}_{\mathrm{ after\ Treatment\ in}\ \left(T-P\right)}+{dY}_{ \mathrm{after\ Placebo\ in}\ \left(T-P\right)}}{2}$$It may be considered as the carry-over effect.Sequence effect (comparison between the results in AB and BA sequences) will be performed by independent sample *t*-test [26].

As a result of a small sample, no further additional analyses (e.g., subgroup and adjusted analyses) will be done.

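### Excluding randomised patients for low drug use in the previous period conflicts with the promised intention-to-treat analysis; any bias depends on who under-uses, and may be nil

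*Protocol article*

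**What the plan says.** The rule is in the protocol article under Follow-up and duration of the study: "they were excluded if they did not have enough adherence and did not use more than 25% of their drug in the previous period". The next sentence deals with patients who choose not to complete. They return to routine clinic care and "will directly be monitored by our pulmonologists they will be excluded from the trial". The same section describes the third of the four visits as "another one after passing the washout period which is the time of being included in the next period".

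Statistical methods states: "The analysis will be done by intention-to-treat and per-protocol". On the test it says: "Treatment effect (comparison between the intervention and control) will be investigated by paired" t-test. The design is a two-period crossover, with periods "each lasting 1 month and separated by a 1-week wash-out period".

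Nothing in the article ties the 25% figure to the per-protocol set, and nothing provides for continued measurement of excluded patients. The sample size section assumes a 2-point gain in %FEV1 on tiotropium, no change on control, 20 patients (10 per sequence) and no drop-out.

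**The concern.** Intention-to-treat keeps randomised patients whatever their drug use. A rule that removes them because of their drug use works against that. An undefined analysis set could be left to the analysis plan. A rule that takes patients out of the trial is different, because no later analysis can recover period 2 outcomes that were never collected.

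The paired t-test needs both periods from each patient. Someone removed at the third visit contributes nothing to it, so for that patient the two planned analyses coincide and the intention-to-treat result no longer serves as a check on the per-protocol one.

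Bias arises if low use depends on treatment. The Adverse events section plans "precise questions about the potentially related adverse effects of the tiotropium which was used in the trial, as xerostomia, pharyngitis", so tiotropium-related effects are expected, and patients who tolerate it poorly could be the ones who stop. The rule is also uneven if applied only at the third visit. It then catches low tiotropium use in the tiotropium-first sequence and low placebo use in the other. A placebo-first patient who under-uses tiotropium in period 2 escapes it.

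**Working it through.** **Inputs from the protocol (Sample size).** Effect 2 points of %FEV1; control change 0; 20 patients, 10 per sequence; 80% power; 5% alpha; no drop-out.

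**Inputs assumed, not in the documents.** Number of removed under-users, k = 1 to 4. Share of the effect kept by a patient low on tiotropium, r = 0 to 0.25. All other patients get the full 2 points. One month is taken as 30 capsules.

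**The plan's own figure.** The protocol gives no figure for under-use, so there is none to reproduce on this point. Its sample size of 20 can be neither confirmed nor refuted, because no within-patient SD is stated. For exactly 80% two-sided power, it implies an SD of the paired difference of about 3.02 points.

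**Threshold.** 25% of 30 is 7.5. Read literally, the rule removes patients who used 7 capsules or fewer. If it was meant as more than 25% missed, it removes those who used 22 or fewer, since 75% of 30 is 22.5.

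**Overstatement.** With m of the removed patients low on tiotropium, the effect in all 20 is 2(20 − m + r·m)/20. The paired estimate without the removed patients is 2.0. The ratio is 20/(20 − m + r·m). A patient low on placebo only still shows the full 2-point difference, so removing that patient does not move the mean.

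| Who is removed | r | k=1 | k=2 | k=3 | k=4 |
|---|---|---|---|---|---|
| All low on placebo only (m=0) | – | 0% | 0% | 0% | 0% |
| Half low on tiotropium (m=k/2, as an average) | 0.25 | 1.9% | 3.9% | 6.0% | 8.1% |
| Half low on tiotropium (m=k/2, as an average) | 0 | 2.6% | 5.3% | 8.1% | 11.1% |
| All low on tiotropium (m=k) | 0.25 | 3.9% | 8.1% | 12.7% | 17.6% |
| All low on tiotropium (m=k) | 0 | 5.3% | 11.1% | 17.6% | 25.0% |

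For the bottom row at k=4, the effect in all 20 is 2 × 16/20 = 1.60, and 2.0/1.60 = 1.25.

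**Under-users in both sequences, rule applied only at the third visit.** Take 4 tiotropium under-users with r = 0, two in each sequence. Only the two in the tiotropium-first sequence are removed. The paired estimate in the remaining 18 is 2 × 16/18 = 1.78, against 1.60 in all 20, an overstatement of 11%.

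**The other reading of the threshold.** If the rule removes patients who miss more than 25%, they may keep much of the effect. With r = 0.75 and all low on tiotropium, the overstatement is 1.3% to 5.3% for k = 1 to 4.

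**Loss of pairs.** This needs no assumption about who under-uses. If 20 patients give exactly 80% power, losing 1, 2, 3 or 4 pairs lowers it to 77.7%, 75.1%, 72.4% or 69.3%.

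**The case against.** The strongest reply is that the sentence is loosely worded and the 25% was meant only for the per-protocol set, where such thresholds normally belong and which Statistical methods names. On that reading no patient is lost. This is possible, and the remedy is then one clarifying sentence. But the rule stands under follow-up, it says patients were excluded, and nothing limits it to an analysis set.

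Two supporting texts are weaker than they look. Table 1 lists "19) No compliance" as an exclusion criterion, but that table governs enrolment, so it is probably a screening criterion. The phrase about exclusion from the trial concerns patients who choose not to complete, a different group. It shows how the section uses the verb, no more. The point does not depend on either.

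A reader might also infer that 1 to 4 under-users would overstate the effect by 4% to 25%. The documents do not support that as a general consequence. It requires every under-user to be low on tiotropium, every one to be removed, and each to keep at most a quarter of the effect. At the third visit, 25% would need 4 of the 10 tiotropium-first patients to have used 7 capsules or fewer, with no tiotropium under-use in the other sequence. The previous period is placebo for about half the patients, so the lower end is 0%.

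Finally, the main change may come late. The abstract reports 20 patients randomised and follow-up due to end in April 2024, the month of publication. That stands, and it is why the fix includes a fallback.

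**Conclusion.** The conflict is real. Followed as written, the rule removes randomised patients for behaviour after randomisation, and the paired t-test then cannot include them in the intention-to-treat comparison. How many patients this affects, and whether it biases the estimate, the documents do not say.

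For up to 4 under-users, the overstatement ranges from 0% (none, or low on placebo only), through about 2% to 11% (half low on tiotropium, keeping 0 to 25% of the effect), to 25% in the extreme case (4, all low on tiotropium, all removed, none of the effect kept). These figures illustrate stated assumptions and do not predict this trial's result. The point is worth correcting because the correction is cheap, not because a large bias has been shown.

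**What to change.** **Follow-up and duration of the study.** State that low drug use does not remove a patient from the trial, its visits or the intention-to-treat set, and only defines the per-protocol set. The sponsor should say whether the threshold is 25% used or 25% missed. The present wording does not settle this, and the choice should not be made on the sponsor's behalf.

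**Statistical methods.** State that intention-to-treat includes all randomised patients by assigned sequence, whatever their drug use.

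**Patients already excluded.** Before unblinding, report their number by sequence. Beside the paired t-test, fit a mixed model with treatment, period and sequence as fixed effects and patient as a random effect, so that their period 1 outcome is kept. This recovers only part of what was lost and assumes that the missing period 2 outcome can be explained by the observed data, so it is a supporting analysis.

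**Cost.** A short clarification in each of two sections, at most one supporting model, and no new visits. Keeping under-users may dilute the intention-to-treat estimate somewhat; the per-protocol analysis already planned complements it.
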